### Oversight of trial sites

Study sites will be required to develop a cluster representation mechanism (CRM) to represent the interests of the cluster (and the individuals within the cluster). The CRM has the same rights as an individual patient in a normal randomised trial; the CRM has the right to withdraw the cluster from the study if it decides that the study is no longer in the interests of the cluster. The CRM includes a Study Gatekeeper (who is responsible for the cluster as a whole, permits the cluster taking part in the study, and monitors the continued involvement of the cluster in the study, for example, with a senior clinician) and a Study Guardian (who is responsible for the individuals in the cluster, permits individuals to take part in the study, and monitors the continued involvement of individuals in the study, for example, a senior nurse). The CRM will be independent of the research team, and will work to a formal document that describes the role of the CRM.

### Inclusion/exclusion criteria for participants and recruitment

Up to 200 patients will be included in the trial. Patients are eligible for inclusion if they have a diagnosis of cancer; are aged 18 years or above; have an estimated prognosis of ≤ 1 week; and are unable to maintain sufficient oral intake (1 L per day, measured/estimated). Patients will be excluded if they are clinically dehydrated; have a relevant advance directive to refuse treatment; have a clinical indication for clinically assisted hydration (for example, hypercalcaemia); have a clinical contra-indication to clinically assisted hydration (for example, cardiac failure); have a clinical contra-indication to peripheral cannulation; are already being administered intravenous fluids/subcutaneous fluids/total parenteral nutrition (TPN)/enteral feeding or fluids; have symptoms of delirium at the time of consent or have experienced symptoms of delirium in the previous 24 hours; or are likely to be transferred to another setting for endof-life care (for example, home, hospice).

Potential participants will be highlighted to the research team by the clinical team; the research team will then screen the patient for eligibility to enter the study. If the patient is deemed to have capacity by the clinical team, then consent will be sought from the patient in the normal manner by the research team Additional file 1.

If the patient is deemed not to have capacity, then a personal consultee (that is, “someone who has a role in caring for the person who lacks capacity or is interested in that person’s welfare but is not doing so for remuneration or acting in a professional capacity”) will be approached for advice re the patient entering the study [24, 25]. In this study, the personal consultee could be a relation of the person or a friend of the person. The personal consultee will be given an information sheet about the study, given the opportunity to ask questions about the study, and asked whether in their opinion the patient would have any objection to taking part in the study.

If the patient is deemed not to have capacity, and no personal consultee is available, then a nominated consultee will be approached for advice re the patient entering the study [24, 25]. In this study, the nominated consultee will be the Study Guardian (who is independent of the research team).

### Interventions

The interventions utilised within this trial represent current standards of care within clinical practice. Sites will be randomised to either ’standard intervention arm A‘ or ’standard intervention arm B‘, and this will become the standard of care within the site for the duration of this trial.

Standard intervention arm A involves:Continuance of oral intake (if appropriate)Regular ’mouth care’Standard management of pain and other symptoms in the terminal phase

Standard intervention arm B involves:Continuance of oral intake (if appropriate)Regular ’mouth care’Standard management of pain and other symptoms in the terminal phaseClinically assisted hydration, that is, parenteral fluids

Mouth care should be performed at least every four hours, and should correspond to the participating site’s policy/procedures for oral care in the terminal phase. Mouth care should be discontinued if it causes distress/discomfort to the patient.

The parenteral fluids may be administered either intravenously or subcutaneously at the discretion of the medical and nursing team [26]. The type of fluid to be administered is dextrose saline (4 % dextrose, 0.18 % sodium chloride), and the volume to be administered will be dependent on the patient's weight [27] Table 1.

### Study procedures

During the treatment period patients will be reviewed at least every four hours, and an assessment made as to whether or not certain symptoms are present, that is, hyperactive delirium (‘terminal agitation‘), pain, excess respiratory secretions (‘death rattle‘), nausea and vomiting, dyspnoea and urinary continence. Agitation will be given a score (see below), but the other symptoms will simply be recorded as present or absent. In addition, changes in regular medications, use of as required (PRN) medications, oral intake, urinary continence, and (if appropriate) parenteral fluids administered, adverse events relating to parenteral fluids and requirements for re-cannulation will also be noted. Data will be obtained from the participant’s observation chart and the participant’s drug chart(s); these documents are considered source documents in this study.

At the end of the study the researcher will record the participant’s outcome, including the date of death/withdrawal, and the reason for withdrawal (if appropriate). The end of study occurs when an individual participant either: a) survives for ≥ 14 days; b) dies (expected outcome); or c) is withdrawn from the study Table 2.

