**Methods/design:**

The study is a cluster randomised trial to assess the feasibility of conducting an adequately powered, randomised controlled trial of clinically assisted hydration in patients with cancer in the last days of life. Twelve sites, four National Health Service (NHS) hospitals and eight NHS/voluntary sector hospices in the United Kingdom, will be randomised to give either standard intervention A: continuance of oral intake and regular mouth care, or standard intervention B: continuance of oral intake, regular mouth care and clinically assisted hydration. Patients will be included if they: i) have a diagnosis of cancer; ii) are aged ≥ 18 yr; iii) have an estimated prognosis of ≤ 1 week and iv) are unable to maintain sufficient oral intake (1 L per day, measured/estimated); and v) are able to give informed consent. Patients will be excluded if they have contra-indications to receiving clinically assisted hydration. The primary endpoint of interest is the frequency of hyperactive delirium (‘terminal agitation‘), and this will be assessed using the Modified Richmond Agitation and Sedation Scale (administered every four hours). Other data to be collected include the frequency of pain, respiratory secretions (‘death rattle‘), dyspnoea, nausea and vomiting, adverse effects to clinically assisted hydration and overall survival. In addition, data will be collected on the use of anti-psychotic drugs, sedative drugs, analgesics, anti-secretory drugs and other end-of-life medication. The study has obtained full ethical approval.

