## Background

The provision of clinically assisted hydration (CAH) at the end of life is one of the most contentious issues in medicine [1, 2], and indeed within the general population [3, 4]. The reasons for contention include: a) the lack of evidence for/against CAH [5, 6]; b) the disparate opinions of healthcare professionals about CAH [7]; and c) the generally positive opinions of patients and their carers about CAH (and the generally negative opinions about withholding/withdrawing CAH) [7]. It is, therefore, unsurprising that the provision of CAH at the end of life is extremely variable within clinical practice (12–88 % of patients with cancer in the last week of life) [8]. It should be noted that, in this instance, CAH refers to the medical provision of parenteral fluids (intravenous, subcutaneous), and not to the medical provision of enteral fluids (such as administering fluids via a gastrostomy/jejunostomy).

**Table 1 Tab1:** Standard treatment B: volume of fluid to be administered

Patient’s weight	Volume of fluid
<45 kg	1 L/24 h
45–60 kg	1.5 L/24 h
>60 kg	2 L/24 h

**Table 2 Tab2:** Overview of study assessments

Assessments	Screening	Treatment period (daily assessments)	End of study
Inclusion/exclusion criteria	X		
Consent	X		
Demographic data	X		
Cancer diagnosis	X		
Concurrent medical history	X		
Regular medication	X	X	
Oral intake	X	X	
Urinary continence	X	X	
4 hourly Modified Richmond Agitation - Sedation Scale scores		X	
4 hourly symptom occurrences		X	
As required medication		X	
Oral intake		X	
Urinary continence		X	
Parenteral fluids administered		X	
Adverse events		X	
Cannulation problems		X	
Participant outcome			X

In 2012, there were 499,331 deaths registered in England and Wales, with cancer being the most common underlying cause of death (29 % total deaths) [9]. There is limited data on the use of CAH in hospitals, and no data on the use of CAH at home or in hospices (although the impression is that CAH is generally not available in the home setting, and is generally not utilised in the hospice setting).

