In 2013, Parry et al. conducted a rapid evidence review of the literature on pathways focussed on the dying phase in end-of-life care and their key components, and concluded that “the current research evidence base is not sufficient to inform specific recommendations to use or not to use clinically-assisted nutrition and/or hydration” [6]. The review included the new randomised controlled trial [16], which again did not address the specific issue of the routine use of CAH at the end of life. Thus, Bruera et al. only included patients with evidence of dehydration, and patients were given relatively low doses of fluid (1 L per day), and the fluids were continued for a variable duration, that is, “until the patient was unresponsive, developed progressive coma, or died”. The conclusion of this study was that “hydration at 1 L per day did not improve symptoms, quality of life, or survival”.

The purported positive effects of CAH include the maintenance of patient comfort (for example, prevention of thirst, prevention of dry mouth), and the maintenance of renal perfusion/prevention of accumulation of toxins and drugs (prevention of delirium, prevention of opioid toxicity) [17]. In contrast, the purported negative effects of CAH include problems due to fluid overload (for example, worsening of peripheral oedema, worsening of cardiac failure), and problems due to fluid-related complications (for example, worsening of vomiting, worsening of respiratory secretions) [17]. In addition, it has been claimed that ketones and other by-products of dehydration can have positive effects on the patients’ condition/symptom control (analgesic effects, sedative effects). As intimated above, there is little evidence to support/refute these effects in the general population.

Patients with cancer may develop a range of problems in the last days of life, including delirium (’terminal agitation’/’terminal restlessness’ [18]), excess respiratory secretions (’death rattle’), urinary retention or urinary incontinence, and continuance or exacerbation of other symptoms (for example, pain, dyspnoea, nausea and vomiting) [19].

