Delirium is one of the most common problems (25–85 % of patients) [20], and one of the most distressing problems (for patients, relatives and healthcare professionals) [21], encountered at the end of life. Dehydration is a recognised cause of delirium, and rehydration a recommended intervention for delirium (in appropriate situations) [20]. Nevertheless, the mainstay of the management of delirium is the use of antipsychotic and/or sedative drugs [20]. Such agents are used in approximately 50 % of patients in the last week of life [22], and although they are generally very effective, they are often associated with untoward sedation (which necessarily impacts the dying process, especially in terms of interpersonal communication). It should be noted that the use of sedative drugs was another major issue raised in the recent review of the LCP (which has resulted in the planned withdrawal of the LCP in the United Kingdom) [10].

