## Discussion

The provision of clinically assisted hydration (CAH) at the end of life is one of the most contentious issues in medicine [1, 2], and indeed within the general population [3, 4]. In some instances there is a clear indication for giving CAH (such as for a patient with opioid toxicity), whilst in other instances there is a clear indication for not giving CAH (for example, in a patient with cardiac failure). Currently, however, it is impossible to make a best interests decision for the majority of patients (due to a lack of evidence). Hence, there is an urgent need/ethical necessity to undertake research to define the role of CAH in the last days of life (and indeed the role of mouth care in the last days of life).

The study interventions to be used in the trial are routinely used in clinical practice, and so all of the patients will receive a ’standard intervention‘ (and not an experimental treatment, or a placebo treatment). Indeed any patients who require a specific intervention or for whom CAH is contra-indicated will not be considered eligible for the trial.

The study team is mindful that the trial involves patients in the last week of life, and it is anticipated that many of the potential participants will be unable to provide informed consent (due to impaired cognition/impaired consciousness). As the study is not a Clinical Trial of an Investigational Medicinal Product (CTIMP), the study comes under the remit of the Mental Capacity Act [24, 25]. Consent will be sought from the patient (whenever possible), or advice sought from a ’personal consultee‘ (when the patient is unable to provide consent), or advice from a ’nominated consultee‘ (when the patient is unable to provide consent, and there is no personal consultee). In this study the personal consultee will be a relation or friend of the patient, and the nominated consultee will be the Study Guardian. It is hoped that this trial will allow a definitive study to be performed of the utility/role of CAH in patients with cancer in the last days of life.

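### Four-hourly symptom checks are coded only present or absent, so rounds in which nausea (and partly pain or dyspnoea) could not be ascertained have no valid code; secondary data only

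*Protocol article*

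**What the plan says.** All references are to the protocol article.

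- **Frequency of checks.** Study procedures sets the schedule in its opening sentence: "During the treatment period patients will be reviewed at least every four hours, and an assessment made as to whether or not certain symptoms are"; it then names what staff are to look for. Follow-up ends at death, at 14 days or at withdrawal. Table 2 carries the same item as "4 hourly symptom occurrences".
- **Coding.** Study procedures: "Agitation will be given a score (see below), but the other symptoms will simply be recorded as present or absent". The list there covers agitation, pain, respiratory secretions, dyspnoea and urinary continence, with nausea and vomiting as one item.
- **Use.** The Abstract says: "Other data to be collected include the frequency of pain, respiratory secretions", followed by dyspnoea and nausea and vomiting. Trial design and setting says that secondary as well as primary endpoint data will serve the design of the later trial.
- **Source.** The data come from the observation and drug charts, and "these documents are considered source documents in this study". Neither chart is shown.
- **Population.** The Discussion anticipates that "many of the potential participants will be unable to provide informed consent (due to impaired cognition/impaired consciousness". The Background says that about half of patients receive antipsychotics or sedatives in the last week of life, and that "they are often associated with untoward sedation".
- **Possible harm of the fluid.** The Background lists among the purported negative effects "problems due to fluid-related complications (for example, worsening of vomiting, worsening of respiratory secretions".

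**The concern.** Nausea is known only if the patient can report it. Pain and dyspnoea depend partly on report and partly on signs. Vomiting and noisy secretions can be seen in anyone. A two-state record suits the last group. It does not suit the first when the patient is unresponsive, because absence and lack of information then share a code or, if the round is left blank, lack of information looks like a missed check. An analysis plan written later cannot fully recover a state that was never charted.

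The share of such rounds could differ between arms. The Background gives prevention of delirium and of opioid toxicity as purported benefits of hydration, and reports a claim that by-products of dehydration are sedating. Both would leave arm B more awake, so it would have more opportunities to report a symptom. An excess of recorded nausea or pain in arm B could then be read as harm from the fluid.

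The joint item adds a separate difficulty. In a responsive patient it means nausea or vomiting; in an unresponsive one it can only mean vomiting. Vomiting is one of the harms that the article names, and it cannot be separated out afterwards.

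**Working it through.** The plan gives no figure on this point, so there is nothing to reproduce. What follows shows direction and order of size only.

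**Inputs.** From the article: two-state coding, and reviews at least every four hours, so 24/4 = 6 rounds a day. Assumed, because the article gives no value: *u*, the share of rounds in which the symptom cannot be ascertained (by arm, *uA* and *uB*), and *p*, the true per-round frequency.

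**1. Per-round frequency, unascertainable rounds coded absent.** If the symptom is equally common in responsive and unresponsive rounds,

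recorded frequency = *p*(1 − *u*), so recorded/true = 1 − *u*.

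The frequency is understated by 10% at *u* = 0.10, 30% at 0.30 and 50% at 0.50.

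**2. Comparison between arms with no true difference.** The recorded B/A ratio is (1 − *uB*)/(1 − *uA*):

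| *uA* | *uB* | B/A ratio |
|---|---|---|
| 0.50 | 0.50 | 0.50/0.50 = 1.00 |
| 0.40 | 0.30 | 0.70/0.60 = 1.17 |
| 0.50 | 0.35 | 0.65/0.50 = 1.30 |
| 0.60 | 0.40 | 0.60/0.40 = 1.50 |

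With *p* = 0.3, the last row is 0.3 × 0.4 = 0.12 in A against 0.3 × 0.6 = 0.18 in B. With equal shares there is no distortion between arms, only understatement in both.

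**3. The same rounds left blank.** The frequency over completed rounds is then *p*(1 − *u*)/(1 − *u*) = *p*, so step 1 does not apply. But *u* cannot be reported, because a missed check and an unresponsive patient look alike.

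**4. 'Ever present' per patient.** Over *R* independent rounds, the recorded proportion is 1 − (1 − *p*)^(*R*(1 − *u*)). Take *p* = 0.05 and *R* = 18 (three days):

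- all rounds ascertained: 1 − 0.95^18 = 0.60;
- *uA* = 0.60: 1 − 0.95^7.2 = 0.31;
- *uB* = 0.40: 1 − 0.95^10.8 = 0.43.

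The gap between arms is the same whether the lost rounds are coded absent or left blank. A 'not assessable' code makes the loss visible but does not remove it from this summary.

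**5. Sensitivity to the main assumption.** Step 1 takes the symptom to be as common in unresponsive as in responsive rounds. At the other extreme, if unresponsive patients do not experience it, 'absent' is correct and nothing is understated. The understatement therefore lies between 0 and *u*.

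**The case against.** A reader might infer that an unresponsive round has to be coded absent, and that the more wakeful arm will therefore look worse. The documents do not support either step as a certainty. The sentence contrasts graded scoring with yes/no recording. It does not say what staff do when they cannot tell, and no denominator is fixed. A round could be left blank or judged from signs. The chart, CRF, full protocol and any analysis plan are not shown. The second step also needs arousal to differ by arm, which the Background makes plausible but nowhere quantifies.

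Further points against the concern:

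- Lack of capacity to consent is not inability to report nausea, and the figure of about half describes drug use, not unresponsiveness. Patients with delirium at consent or in the previous 24 hours are excluded. This stands: the evidence supports 'often', not a number.
- The mRASS is charted on the same four-hourly schedule and has sedation in its name, so unresponsive rounds might be identifiable already. This stands in part. Outcome measures describes only the agitation levels, and no such use is planned.
- Analysing assessable rounds conditions on a state that arises after randomisation and that treatment may affect. This stands, and it is why that figure should not replace the all-rounds figure.
- The primary endpoint rests on mRASS scores and drug treatment, and the later trial's sample size on delirium proportions and between-cluster variation. This stands: neither is touched.
- Fluid-related adverse events are recorded separately, which gives another route for vomiting. This stands only for vomiting that someone attributes to the fluid.

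What the objection does not remove is the stated rule itself. A condensed article may leave detail to other documents, but here it fixes a two-state code, and a third state on an unseen chart would depart from it.

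**Conclusion.** The point holds in a limited form. The article fixes a coding rule with no valid entry for a round in which nausea, and in part pain or dyspnoea, could not be ascertained, in a population where it expects such rounds. They may be recorded as absent, or left blank and be indistinguishable from missed checks. Understatement follows if they are recorded as absent and the symptom does occur in unresponsive patients. Distortion between arms needs, in addition, a difference in arousal.

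The size is unknown. The ratios of 1.17 to 1.50 rest wholly on chosen shares, and equal shares give 1.00. Agitation, secretions, vomiting and continence do not need the patient's report, so the problem does not extend to every symptom check. Only secondary data are affected. This is a worthwhile, inexpensive improvement, not a threat to the trial's main purpose.

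**What to change.** In Study procedures, and on the four-hourly chart, CRF and eCRF:

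1. Add a 'not assessable' code for nausea, pain and dyspnoea, used when the patient cannot report and no sign is observed.
2. Report the share of non-assessable rounds by arm. How often these symptoms can be assessed is itself a feasibility result.
3. Show each symptom's frequency twice: over all rounds, with non-assessable rounds counted as not present, and over assessable rounds. State that the second conditions on a post-randomisation state. It may also lean high for pain and dyspnoea, since an unresponsive round with a visible sign stays in the denominator and one without leaves it. State too that neither display fully corrects an 'ever present' summary.
4. Record vomiting separately from nausea.
5. For participants recruited before the change, use same-round mRASS sedation levels, if they are charted, to identify unresponsive rounds.

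**Cost.** A wording change to the chart, CRF and eCRF and a short note to sites; no extra visits, staff or patients, and no change to care. Recruitment began on 20 February 2015 (Trial status), so earlier participants keep the two-value coding and must be flagged. The assessable-round denominators will be smaller. If the chart already carries such a code, the change reduces to correcting the article's sentence, reporting the share and, if it is not already done, splitting the joint item.
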